### **12.5. Safety analysis:**

The proportion of patients presenting at least one AE will be described. The incidence rate and 95% confidence interval per study group will be presented. Otherwise, only descriptive statistics will be presented. Laboratory safety parameters (hematology and biochemistry) will also be described individually for each study group, showing the proportion of patients by degree of elevation relative to ULN and to baseline values and changes in blood levels over time.

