| STUDY DESIGN: This is a proof-of-concept Phase II clinical trial with three different groups: two groups will receive antichagasic therapy plus 40 or 80 mg/day of ATO, respectively. The third group will receive a placebo plus antichagasic therapy. Patients will first receive conventional antichagasic treatment for two months. After a washout of two weeks (or until normalization of liver enzymes), treatment with atorvastatin or placebo will be initiated for two months. These doses were chosen to minimize false negative results, thus providing the best hypothesis test and maximizing the pharmacodynamic effect on inflammation and cardiac and endothelial function. In addition, the treatment sequence aims to minimize adverse reactions that could be caused by the eventual combination of antichagasic drugs with atorvastatin. Study subjects will be randomized, and the three groups will be double-blinded (both clinical investigators and subjects will be blinded) to ATO or placebo. However, antichagasic therapy will be open-label. In addition, qPCR and the other laboratory evaluations, as well as ECG and 2D echocardiograms, will be performed with the clinical investigators blinded to ATO or placebo allocation.

As mentioned above, this study will be conducted at four centers: 1) Hospital San Juan de Dios and 2) Hospital Felix Bulnes in Santiago, Metropolitan Region, 3) Hospital [name] in Viña del Mar, and |

4) Hospital San Martin de Quillota, Valparaiso Region.

**ABSTRACT:** Cardiac complications, including heart failure and arrhythmias, are major causes of disability and death in Chagas disease (CD). We postulate that statins ameliorate vascular and cardiac inflammation in patients with chronic CD, contributing to the recovery of endothelial and cardiac function and thereby improving the efficacy of antichagasic therapy.

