### Efficacy analysis:

**Hypothesis:** Atorvastatin, in combination with conventional antichagasic therapy of nifurtimox or benznidazole, improves cardiac function in subjects with asymptomatic chronic-phase Chagas disease compared with placebo.

For analysis of the **primary outcome**, a one-sided Fisher's exact test of the proportion of patients with a significant decrease in biomarker levels in the ITT (primary analysis), and per protocol (secondary analysis) populations will be used. ANOVA test will be performed to analyze differences in variances between the different markers.

An exact test will be performed for all secondary comparisons of proportions between ATO versus placebo, including parasitological response to treatment. Latent class and multivariate analyses will assess parasitological response, biomarker changes, and ATO dose association.

If there are no significant differences between ATO treatments, these data will be collapsed into a single comparison group to obtain greater precision in the treatment effect estimate, given that this is a proof-of-concept study for statins as a class. In this case, no adjustment for multiple comparisons will be made.

**Safety Analysis:** Clinical assessments, electrocardiograms, and laboratory tests will be used to monitor the safety and tolerability of the drugs under study throughout the observation period of the subjects.

The proportion of patients presenting at least one AE will be described. The incidence rate and 95% confidence interval per study group will be presented. Otherwise, only descriptive statistics will be presented. Laboratory safety parameters (hematology and biochemistry) will also be described individually for each study group, showing the proportion of patients by degree of elevation relative to ULN and to baseline values and changes in blood levels over time.

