## 8.2. Secondary goals:

8.2.1. To evaluate the efficacy of the combination of ATO and antichagasic therapy to decrease:

- Inflammation, as measured by plasma levels of the cytokines, TNF- $\alpha$ , IFN- $\gamma$ , IL-10, IL-1B, IL-4, and IL-17A.
- Endothelial activation, as measured by plasma levels of sCAM: sE-selectin, sICAM-1, and sVCAM-1.
- Cardiac damage and function: measured by plasma levels of BNP, cTnT, 12-lead resting ECG (heart rate, QT segment duration, and electrical conduction changes determined by QRS segment duration and morphology), and 2D echocardiogram (ejection fraction).

8.2.2. To determine the safety and tolerability of the combination of ATO with antichagasic therapy, measured by the incidence of AEs (e.g., rhabdomyolysis) and treatment discontinuation.

8.2.3. To evaluate the treatment response to the combination of ATO with antichagasic therapy, as measured by quantitative PCR and serology, over a 10-month follow-up period.

8.2.4. To determine the degree of therapy adherence by measuring drug accountability throughout the study.

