## 9.3. Study description:

This is a proof-of-concept Phase II clinical trial with three different groups: Two groups will receive antichagasic therapy plus 40 or 80 mg/day of ATO. The third group will receive a placebo plus antichagasic therapy. The placebo is justified as long as the patient receives the complete conventional antichagasic treatment; therefore, the management of his Chagas disease is assured. In this clinical trial, the placebo will be a nutritional supplement tablet with an appearance similar to that of ATO. This product was chosen given the potential difficulties in manufacturing a small number of pills since the trial does not have a pharmaceutical industry sponsor capable of manufacturing it under Good Manufacturing Practice standards.

Nutritional supplements do not affect vascular or cardiac inflammatory parameters and therefore do not introduce confounding elements in the comparative analysis with atorvastatin.

Patients will first receive conventional antichagasic therapy for two months. After two weeks (or until normalization of liver enzymes), treatment with atorvastatin or placebo will be initiated for

four months. These doses were chosen to minimize false negative results, thus providing the best hypothesis test and maximizing the pharmacodynamic effect on inflammation and cardiac and endothelial function. In addition, the treatment sequence aims to minimize adverse reactions that could be caused by the eventual combination of antichagasic drugs with atorvastatin. Study subjects will be randomized, and the three groups will be double-blinded (both clinical investigators and subjects will be blinded) to ATO or placebo. However, antichagasic therapy will be open-labeled. In addition, qPCR and the other laboratory evaluations, as well as ECGs and 2D echocardiograms, will be performed with the clinical investigators blinded to ATO or placebo allocation.

This study will be conducted in four centers: 1) Hospital San Juan de Dios and 2) Hospital Felix Bulnes in Santiago, Metropolitan Region, 3) Hospital [name] in Viña del Mar, 4) Hospital San Martin de Quillota, Valparaiso Region. Each center annually admits 60 new patients to its Chagas Control Program (CCP). These four centers are part of the care network of the National Chagas Disease Control Program.

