#### **9.5. Duration of the study and duration of subject participation:**

The total duration of patients' participation in the study will be twelve months, considering two weeks for screening and evaluation according to PCC guidelines and eight weeks of treatment with the antichagasic drugs. The administration of ATO and placebo will continue for an additional eight weeks in their respective groups. There will be follow-up visits up to 12 months after the start of treatment (see appendix for a graphical presentation of the study design).

Following voluntary written informed consent, patients will begin a 14-day evaluation phase. Once the patient is randomized and treatments are initiated, they will have follow-up visits during the treatment phase of the study on days 30, 60, 120, and 180, with a two-week rest period or until normalization of liver enzyme levels ( $\pm$  four-day allowable window), and three visits after the end of treatment (EOT) on days 180, 240 and 360 ( $\pm$  14-day allowable window). In addition, patients will be advised to return on any day during the follow-up period if they have any medical incidents or AEs.

Recruitment is expected to be completed within 24 months from the start of recruitment. Therefore, the time frame between the first patient entering (FPI) and the last patient leaving (LPO) is 36 months. However, the total duration of the study is estimated at 48 months, from the initiation phase to the final study report.

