#### **11.2. Adverse events and withdrawal from the study**

##### **11.2.1. Adverse events:**

An AE will be defined as any adverse medical event (any unfavorable and unintended symptom, sign, or disease, including an abnormal laboratory or ECG finding) or worsening of any pre-existing condition occurring during the study, whether or not considered causally related to the study or study drugs. Abnormal laboratory (hematology and biochemistry) results will be reported as an AE if they: a) occur or worsen after initiation of study treatments, b) are considered a clinically significant adverse change by the clinical investigator, or c) are higher than Common Terminology Criteria for AEs (CTCEA) grade 1 (National Cancer Institute (USA), 2017), unless associated with an already reported clinical AE.

Clinical investigators, or appropriate site personnel (not involved in the study), will screen any subject experiencing an AE as soon as possible. The investigator will do whatever is medically necessary for the safety and well-being of the subject. The subject will remain under observation while receiving any trial drug and for two months following the last day of drug administration, or longer if medically indicated in the investigator's opinion. All AEs observed or reported after administration of investigational treatments will be followed until resolved or until medically stable.

For this study, the clinical investigators at each center will report to the principal investigator, who, in turn, will be responsible for reporting AEs to the Ethics Committees of the Centers and the Human Research Ethics Committee of the Faculty of Medicine of the University of Chile and the clinical trials section of the ISPCH. Clinical investigators should report all directly observed AEs and all those spontaneously reported by subjects, using concise medical terminology. In addition, during each trial visit, subjects will be interviewed and undergo a specific physical examination for the evaluation of AEs. All adverse events should be recorded in the subject's clinical record and an ad hoc database.

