### **12.3. Populations to be analyzed:**

Three populations will be included in the analysis: i) the intention-to-treat (ITT) population comprising all patients randomized by their assigned treatment groups, ii) the per-protocol population comprising all ITT patients without any significant deviation from protocol, and iii) the safety population comprising all patients randomized and having received at least one dose of study treatment.

Descriptive statistics for demographic data and baseline characteristics will be presented for the per-protocol and ITT populations.

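### The by-arm adverse-event summary includes ten weeks or more of antichagasic therapy and washout before any atorvastatin dose, which dilutes the atorvastatin–placebo contrast

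*Protocol*

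**What the plan says.** **Sequence.** Randomisation is at day 0 (schedule in section 9.6). Section 9.5 puts the visits after that point: "Once the patient is randomized and treatments are initiated, they will have follow-up visits during the treatment phase of the study". Nifurtimox (NFX) or benznidazole (BZD) is given first. The Summary (section 6) continues: "After a washout of two weeks (or until normalization of liver enzymes), treatment with atorvastatin or placebo will be initiated for two months". Section 9.3 has the same order but gives atorvastatin (ATO) or placebo for four months. It also gives the reason for the order: "the treatment sequence aims to minimize adverse reactions that could be caused by the eventual combination of antichagasic drugs with atorvastatin".

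**What counts as an AE.** The definition in section 11.2.1 extends to "worsening of any pre-existing condition occurring during the study, whether or not considered causally related to the study or study drugs". Laboratory abnormalities can count once study treatments have begun, and the first of these is NFX or BZD. The Summary says that clinical, ECG and laboratory assessments "will be used to monitor the safety and tolerability of the drugs under study throughout the observation period of the subjects".

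**Who is counted.** Section 12.3 defines "the safety population comprising all patients randomized and having received at least one dose of study treatment".

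**What is reported.** Section 12.5: "The proportion of patients presenting at least one AE will be described. The incidence rate and 95% confidence interval per study group will be presented". Everything else is descriptive.

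**What it serves.** Section 8.2.2 gives the objective: "To determine the safety and tolerability of the combination of ATO with antichagasic therapy, measured by the incidence of AEs (e.g., rhabdomyolysis) and treatment discontinuation". Among the additional measures, section 9.1(e) lists stopping treatment because of severe AEs, without saying which drug was stopped.

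**The concern.** The arms differ only from the first ATO or placebo dose. Before that, all patients receive the same open-label therapy, which section 7.1.4 describes as toxic. A patient who has any AE on NFX or BZD already counts as a case in the share with at least one AE, so a later AE on ATO adds nothing to that share. An event rate counted from day 0 is diluted in another way: the same early events and early time enter every arm.

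If *study treatment* in section 12.3 includes NFX and BZD, patients who stop before ever taking ATO or placebo also sit in the ATO arms. The discontinuation measure in 9.1(e) can likewise be filled by NFX or BZD stoppages. At stake is how clearly the trial can describe what ATO itself adds in harm.

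**Working it through.** **No figure to reproduce.** The protocol gives no expected AE rate and no safety power, so the check is of timing and dilution.

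**Time before ATO or placebo.** NFX/BZD lasts 60 days (section 7.1.4) or eight weeks = 56 days (section 9.5). The gap is at least 14 days and longer if liver enzymes have not normalised.
- 60 + 14 = 74 days, or 56 + 14 = 70 days.
- Share of the treatment span if ATO lasts two months: 74/(74 + 60) = 55%.
- Share if it lasts four months: 74/(74 + 120) = 38%.
- Share of the 360-day observation: 74/360 = 21%.

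**At least one AE.** Let b be the risk before ATO or placebo, equal across arms in expectation because of randomisation. Let q1 (ATO) and q0 (placebo) be the later risks among patients with no earlier AE.
- P = b + (1 − b)q in each arm.
- Difference = (1 − b)(q1 − q0).

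This needs no independence between phases. Reading q as the risk among all who start ATO or placebo does, and I assume it below.

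**Inputs that are assumptions.** q1 = 30%, q0 = 15% and every value of b. Two values of b borrow figures from section 7.1.4: 16.2% (serious AEs on treatment) and 48% (upper figure for forced discontinuation on NFX). Neither is an any-AE rate.

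| b | ATO | Placebo | Difference |
|---|---|---|---|
| 0 (ATO/placebo phase only) | 30.0% | 15.0% | 15.0 points |
| 16.2% | 41.3% | 28.8% | 12.6 points |
| 30% | 51.0% | 40.5% | 10.5 points |
| 48% | 63.6% | 55.8% | 7.8 points |

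For 20% against 10%, the 10 points become 8.4, 7.0 and 5.2.

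**Patients who never start.** If they stay in the arms and make up 25% (section 12.1's dropout figure, used here as an assumption, and independent of earlier AEs), the difference at b = 30% is 0.75 × 0.70 × 15 = 7.9 points.

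**A rate per person-time.** Section 12.5 does not define its incidence rate. If it is events over time from day 0, with equal early rates and equal time in each arm, the rate difference keeps the fraction (time after ATO start)/(total time). Over the treatment span that is 60/134 = 45% or 120/194 = 62%.

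**Is a split worth a smaller denominator?** Wald 95% interval for the difference: d ± 1.96 √[P1(1 − P1)/n + P0(1 − P0)/n].
- ATO/placebo phase only, 75 starters per arm: √[(0.21 + 0.1275)/75] = 0.067, giving 1.9 to 28.1 points.
- Whole study, 100 per arm, b = 30%: √[(0.2499 + 0.2410)/100] = 0.070, giving −3.2 to 24.2 points.

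Under these assumptions the phase-specific summary is clearer even with a quarter fewer patients. The intervals only show scale, because section 12.5 plans an interval for each arm and none for the difference.

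**The case against.** The strongest case against is that recording AEs from the first treatment is normal, that section 12.5 names no window, and that an analysis plan not shown here may define AEs by phase. The whole-study figure by randomised arm is also an unbiased description of the full regimen, which is how section 8.2.2 frames the objective. This stands in part: nothing forbids a split, and the whole-study table deserves to stay. But the protocol itself fixes the AE definition, the safety population and the summary measure, and read together they point to the whole study.

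Several stronger readings are tempting and not supported:
- **The safety comparison is biased.** It is not. Early AEs fall equally on the arms in expectation.
- **A safety test loses power.** Section 12.5 plans no ATO-versus-placebo test of AEs.
- **Statin toxicity would be hidden.** CK and liver enzymes are measured at every visit and described against baseline and over time (sections 9.6 and 12.5), events are graded (11.2.3), and causality weighs timing (11.2.4). Rhabdomyolysis, if rare on NFX and BZD, is little diluted.
- **Patients who never start ATO certainly enter the safety population.** *Study treatment* is ambiguous: the Summary lists only ATO as investigational, while section 11.1.1 uses study medication more widely.
- **The words combination and coadministration are a defect in themselves.** The sequence and its reason are stated openly, so this is only wording.

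**Conclusion.** The point holds as dilution of one crude but prominent measure. As sections 11.2.1, 12.3 and 12.5 stand, the by-arm AE summary covers about 70 to 74 days or more before any ATO or placebo dose. The period follows from the protocol's own text, and so does the direction of the effect, given any AE risk on NFX or BZD. The size does not: b and the later AE rates are assumed. If the 16.2% and 48% of section 7.1.4 applied here, the any-AE risk would be at least as high, but they are not estimates of it. Over that range an assumed 15-point difference falls to between 12.6 and 7.8 points. A person-time rate from day 0 is also diluted, by a different factor. The harm is to estimation only. This is a worthwhile improvement, not a threat to the trial's validity.

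**What to change.** - **Sections 12.3 and 12.5:** tabulate AEs and discontinuations separately for the antichagasic phase (day 0 to the first ATO or placebo dose) and the ATO/placebo phase.
- **By-arm ATO safety summary:** use AEs with onset on or after the first ATO or placebo dose, in patients who took at least one such dose. Keep the whole-study table as a supplement.
- **Section 12.3:** say whether *study treatment* includes NFX and BZD.
- **Section 9.1(e):** record which drug was stopped.

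**Cost.** Some protocol wording and one split of the tables, with no added visits or patients. Section 11.2.2 has the SAE report carry the onset date and says the CRF collects the same data. The date of the first ATO or placebo dose must also be on record, since the gap varies with liver enzymes. The denominator becomes smaller: with 75 instead of 100 per arm, the interval for 30% against 15% widens from 3.6–26.4 to 1.9–28.1 points. Restricting to starters also relies on the blind holding until that first dose. Section 12.2 delivers the package after enrolment, so it may be in hand before then, and the placebo is a look-alike supplement tablet (section 9.3). Reporting the number and reasons for not starting, by arm, would let a reader check this.

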#### **7.1.4. Treatment of chronic chagasic cardiomyopathy and strategies of improvement:**

In Chile, etiologic treatment of CD is with 5-10 mg/kg/day of nifurtimox (NFX) or 5 mg/kg/day of benznidazole (BZD) for 60 days (MINSAL, 2017). All patients should receive antichagasic treatment without exclusion or delay, except during pregnancy and lactation, although there is recent evidence suggesting that NFX may be safe in these conditions (Moroni et al., 2019). Also, hypersensitivity to trypanocidal drugs excludes its use. Other exclusions are severe renal, hepatic, or cardiac disease, including CCC with structural compromise, alcoholism (Antabuse effect of NFX), and severe megacolon or megaesophagus (MINSAL, 2017).

Treatment of CD is associated with an increased risk of serious adverse events (AEs), with a mean incidence of 16.20% (PAHO, 2018), a situation that may force discontinuation of therapy in up to 48% of patients receiving NFX (Crespillo-Andujar et al., 2018a; Crespillo-Andujar et al., 2018b; Jackson et al., 2020). AEs include weight loss greater than 5-15%, digestive disorders (nausea, vomiting, diarrhea, epigastralgia and dyspepsia, abdominal distension), headaches, irritability, insomnia, mood disorders, memory loss, fever, arthralgias, myalgias, severe or significant skin and mucosal rashes such as Stevens-Johnson syndrome, evidence of thrombocytopenia, pancytopenia or signs of bone marrow depression, elevated transaminases, leukopenia below 2500/mm^3, CNS disorders such as paresis, paralysis or seizures, and behavioral changes, especially in the case of NFX.

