## **8. OBJECTIVE AND GOALS OF THE TRIAL**

### **8.1. Primary Goal:**

To evaluate the use of atorvastatin, in combination with antiparasitic therapy (NFX or BZD), is safe and more effective than antiparasitic therapy alone in preventing the occurrence of cardiac disturbances by reducing overall inflammation and in improving endothelial and cardiac functions.

To assess the primary endpoint, the number of patients with a change in the stage of chronic cardiomyopathy in 12 months from the beginning of antichagasic treatment will be considered.

We will evaluate whether the effect of atorvastatin in combination with antiparasitic treatment (NFX or BZD) is more effective than antiparasitic therapy alone (placebo group) in preventing the appearance of cardiac disorders determined by non-progression from stage A according to the First Latin American Guidelines for the diagnosis and treatment of chagasic cardiomyopathy (Andrade et al, Arq Bras Cardiol 2011;97 Suppl 3:1-48.) To make this assessment, significant changes in i) electrocardiogram (heart rate and QT interval duration, as well as the appearance of electrical conduction disorders, determined by QRS segment duration and morphology), ii) ejection fraction

(assessed by echocardiography), and iii) cardiac silhouette size (chest X-ray) will be taken into account

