### **12.4. Efficacy analysis:**

For analysis of the primary outcome, a one-sided Fisher's exact test of the proportion of patients with a significant decrease in biomarker levels in the ITT (primary analysis) and per protocol (secondary analysis) populations will be used. ANOVA test will be performed to analyze differences in variances between the different markers. An exact test will be performed for all secondary comparisons of proportions between ATO versus placebo, including parasitological response to treatment. Latent class and multivariate analyses will assess the association between parasitological response, biomarker changes, and ATO doses.

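### Safety of adding atorvastatin is a stated goal, but section 12.5 plans only per-group rates and names no estimate of the atorvastatin-minus-placebo difference

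*Protocol*

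**What the plan says.** Protocol 8.1 sets out to show that atorvastatin with antiparasitic therapy "is safe and more effective than antiparasitic therapy alone in preventing the occurrence of cardiac disturbances". Protocol 8.2.2 adds a secondary goal: "To determine the safety and tolerability of the combination of ATO with antichagasic therapy, measured by the incidence of AEs", and by treatment discontinuation.

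Protocol 12.5 describes the proportion of patients with at least one adverse event and then states: "The incidence rate and 95% confidence interval per study group will be presented. Otherwise, only descriptive statistics will be presented". Laboratory safety values "will also be described individually for each study group, showing the proportion of patients by degree of elevation relative to ULN" and to baseline. The safety paragraph of the Summary repeats the restriction: "Otherwise, only descriptive statistics will be presented".

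Protocol 12.4, headed as the efficacy analysis, contains this sentence: "An exact test will be performed for all secondary comparisons of proportions between ATO versus placebo, including parasitological response to treatment".

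The Summary and section 9.3 give the sequence. Antichagasic treatment comes first, for two months, in every arm. After a gap of two weeks, or until liver enzymes normalise, atorvastatin or placebo starts. Section 11.2.1 counts as an adverse event anything adverse that occurs during the study, whatever its cause.

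**The concern.** The practical safety question is what atorvastatin adds to a background that every patient receives. The randomised, blinded placebo arm is there to answer it, yet the safety analysis names no quantity that uses that arm as a comparator. The text is not merely silent in a way that a statistical analysis plan could fill: the word "only" in "Otherwise, only descriptive statistics will be presented" restricts what will be presented, so a later plan that added a between-arm interval would depart from the protocol.

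The background is also toxic. Section 7.1.4 associates antichagasic treatment with an "increased risk of serious adverse events (AEs), with a mean incidence of 16.20" per cent, and with discontinuation in up to 48% of patients on nifurtimox. Those events belong to the first two months, before any atorvastatin is taken, but they count towards each arm's whole-study proportion. At stake is whether the report can say how large an excess harm the data rule out.

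**Working it through.** **1. The passages side by side.** The protocol states no safety figure to reproduce, so the first check is textual.

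- Sections 8.1 and 8.2.2 make safety of the combination a goal, measured by adverse event incidence and discontinuation.
- Section 12.5 and the Summary give a rate and interval per group, with description for the rest. No difference, ratio or test is named.
- Section 12.4 gives an exact test for all secondary comparisons of proportions, atorvastatin versus placebo. The adverse event and discontinuation proportions of 8.2.2 are secondary proportions, so a literal reading includes them. The heading and the one named example, parasitological response, point to efficacy only.

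Either 12.4 excludes safety, and no between-arm safety analysis is planned, or it includes safety, and it conflicts with the restriction in 12.5. In both cases no estimate or upper limit for the difference is specified.

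**2. What the whole-study proportion measures.** Let *a* be the probability of at least one event in the antichagasic phase, equal in both arms, and let *b0* and *b1* be the probabilities of at least one event after placebo or atorvastatin starts. If the phases are independent within a patient (an assumption), then

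P(at least one event) = 1 − (1 − *a*)(1 − *b*), so the whole-study difference = (1 − *a*)(*b1* − *b0*).

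Take an assumed excess of 10 points after atorvastatin starts:

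- *a* = 0.162: (1 − 0.162) × 10 = 8.4 points.
- *a* = 0.48: (1 − 0.48) × 10 = 5.2 points.

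The values of *a* are borrowed from section 7.1.4 for scale. They refer to serious events and to nifurtimox discontinuation, not to events of any kind. The shared first phase raises both arms' proportions and shrinks the visible difference.

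**3. Precision of a between-arm interval.** The inputs are 100 per group recruited, or 75 after the 25% dropout (section 12.1), and an assumed event rate of 16.2% in both arms. Simple Wald half-widths are:

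- Per arm, as planned: 1.96 × √(0.162 × 0.838 / 100) = 7.2 points.
- Difference, 100 versus 100: 1.96 × √(2 × 0.162 × 0.838 / 100) = 10.2 points.
- Both doses pooled, 200 versus 100: 1.96 × √(0.162 × 0.838 × (1/100 + 1/200)) = 8.8 points.
- Difference, 75 versus 75: 1.96 × √(2 × 0.162 × 0.838 / 75) = 11.8 points.

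Over assumed rates of 5% to 48%, the half-width for a difference runs from 6.0 to 13.8 points with 100 per arm, and from 7.0 to 16.0 points with 75 per arm.

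**The case against.** Four points on the other side deserve weight.

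*The goal does not expressly make safety comparative.* This stands. A reader might infer from 8.1 that safety is to be judged against antichagasic therapy alone, but the comparator attaches grammatically to effectiveness. The sentence in 8.1 that names the placebo group asks only whether the combination "is more effective than antiparasitic therapy alone (placebo group) in preventing the appearance of cardiac disorders". Goal 8.2.2 names no comparator, and a per-arm incidence answers it as worded. The case rests on what is needed to interpret the safety of an added drug, not on a contradiction between goal and analysis.

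*The arms are not left uncompared.* This also stands. A reader might infer that atorvastatin and placebo are never contrasted on safety. The documents do not support that: 12.5 reports the placebo arm on the same measures as both atorvastatin arms, a difference can be computed from the reported counts, and 12.4 may cover these proportions.

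*Descriptive safety is usual in a phase II proof-of-concept trial, and interval methods belong in a statistical analysis plan.* This stands in part. The choice of interval can wait for that plan. The restriction to description cannot, because it is protocol text.

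*The harm from reading per-arm intervals is hypothetical.* This stands. A reader might infer that safety will be judged by whether the groups' intervals overlap, and calculate how often that would miss a real excess. The protocol states no such rule, so such figures would not describe this plan. Nor does any figure in the protocol fix the size of an excess: section 7.2 cites a low incidence of severe events for atorvastatin.

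**Conclusion.** The point holds as a specific, inexpensive improvement. Section 12.5 and the Summary confine safety to per-group rates and description, name no atorvastatin-minus-placebo estimate, and leave their relation to the exact tests of 12.4 unclear. Because every arm has two months of antichagasic treatment first, a whole-study proportion with at least one adverse event does not isolate atorvastatin.

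The size is a matter of precision. At an assumed 16.2% in both arms, the trial could bound the difference to about ±10 points with 100 per arm, or about ±9 points with the doses pooled. That is coarse and would often include zero for a modest excess, but it states plainly what has and has not been ruled out. The figures rest on equal event rates in both arms, the Wald approximation and the borrowed 16.2%; the 5% to 48% range shows how far they move. The point does not affect the efficacy analysis.

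**What to change.** In 12.5 and in the safety paragraph of the Summary, replace the sentence that limits the rest to descriptive statistics with a between-arm estimate:

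- **Contrasts:** the risk difference with its 95% confidence interval for 40 mg versus placebo, 80 mg versus placebo, and both doses pooled versus placebo.
- **Measures:** at least one adverse event, at least one serious adverse event, discontinuation due to an adverse event (stating which drug was stopped), and the CK and ALT elevation categories that 12.5 already tabulates.
- **Periods:** the whole study, and separately events that start on or after the first dose of atorvastatin or placebo, among patients who took at least one such dose. The protocol gives the atorvastatin period as two months in the Summary, eight weeks in 9.5 and four months in 9.3. Those passages must be reconciled, but a split at the first dose works whichever stands.
- **Status:** label the intervals as estimation, not hypothesis tests, and keep the per-arm rates beside them.

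In 12.4, state whether the exact tests cover adverse event and discontinuation proportions, so that 12.4 and 12.5 agree.

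The cost is a wording change in two or three places and some extra table columns. No extra patients or visits are needed; start dates of events and of atorvastatin or placebo must be available for the split. The downside is several unadjusted intervals, one or more of which may exclude zero by chance.
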